#### Electrocardiography

A standard 12-lead ECG is performed with the CardioTouch 3000-S for each study subject by employing strictly standardized procedures. Research staff members were trained to properly place electrodes. At least 4 cardiac cycles are taken from each of 12 leads. The machine runs at 50 mm/sec. The following ECG parameters are evaluated by a trained clinical researcher: waves and complexes, presence and description of ECG abnormalities including pathologic q-waves, ST elevation, ST depression, T-wave inversion, hypertrophy, QRS axis deviation, block, and arrhythmia. ECGs were visually inspected for technical errors and were interpreted by a qualified cardiologist. The prevalence of specific ECG abnormalities as well as grouped abnormalities will be reported for each study group. Associations between COPD and ECG abnormalities, crude and adjusted by sex, age, and smoking status, will be measured and presented.

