## Methods

### Study Design

This is an observational study with a cross-sectional design to assess the prevalence of COPD in Almaty, Kazakhstan, among individuals aged 40 to 59 years based on results of spirometry, the presence of structural changes in the lungs, and symptoms of COPD.

The study population is 3 groups of male and female residents of Almaty, the largest city in Kazakhstan, with a population of 1.7 million people, 9% of whom are aged 40 to 59 years. Members of the first group include current smokers with more than a 10 pack-year history of smoking (smokers). The second group comprises individuals who quit smoking from 1 to 5 years ago and have more than a 10 pack-year history of smoking (ex-smokers). The third group comprises persons who have never smoked regularly (ie, smoked less than 100 cigarettes in their lifetime) (never-smokers).

We recruited individuals who are 40 years of age or older because most people are at least 40 years old when the symptoms of COPD first appear [23]. The same age limit is selected for many COPD prevalence studies [24-26]. The upper age was set at 59 years to avoid survival bias [27] possibly leading to underestimating the effects of risk factors on COPD. We have taken into account that the life expectancy at birth among males was only 66 years in Kazakhstan in 2015 [28].

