#### Questionnaire

The questionnaire was designed to collect data on possible COPD risk factors including history of smoking; current smoking; level of smoking exposure (in pack-year); passive smoking; and occupational and environmental hazards including dusts, chemicals, and indoor fuel pollution. The questionnaire contains the following covariates: age, gender, ethnicity, education, occupation, and self-reported morbidity. CAT is used to collect Information about COPD symptoms. The test was designed and validated for use in routine clinical practice to evaluate the health status of patients with COPD [41]. Computer-assisted personal interviewing (CAPI) with tablets has been implemented to collect, store, and transmit data related to a personal survey interview.

The questionnaire was piloted by interviewing 7 testers—3 smokers, 2 ex-smokers, and 2 never-smokers. After completing pilot interviews, the testers were asked to answer specific questions and then provide comments and suggestions on the whole questionnaire. The questions that were not clear enough were identified and have been improved.

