### Statistical Analysis

Data from all CAPI devices will be exported to one database, and R version 3.3.1 (The R Foundation) will be used for data analysis. Descriptive analyses will be performed using mean, median, interquartile interval, and standard deviation for quantitative variables and frequency tables for categorical variables. Depending on the nature of outcome and exposure variables, type of data distribution, and the sample size, bivariate comparisons will be made by the following tests: chi-square test, Fisher’s exact test, analysis of variance, *t* test, and the Mann-Whitney test.

A multivariable analysis (generalized linear models) will be conducted to control for confounding. Presence of effect modification/interaction terms will be explored. An alpha <.05 will be considered significant. To construct the optimal model, backward elimination will be used. The full models will contain all independent effects and some important interactions. Mediators (variables that lie on the causal pathway between exposure and outcome) will not be included in the model. To avoid multicollinearity, we will examine the tolerance for each independent variable. If the tolerance value is less than 0.1, we will omit a variable from the analysis. The optimal model will be defined based on the Akaike Information Criterion. Model diagnostic plots will be generated to test model assumptions (eg, normality of deviance residuals).

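### The named adjustment set for the COPD-ECG associations carries smoking only as a three-level status, although pack-years are collected and could be added at almost no cost

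*Protocol article*

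**What the plan says.** - **Electrocardiography** promises COPD-ECG associations "crude and adjusted by sex, age, and smoking status, will be measured and presented". No other adjustment variable is named there.
- **Questionnaire** lists, among possible COPD risk factors and separately from past and current smoking, "level of smoking exposure (in pack-year); passive smoking; and occupational and environmental hazards". The Abstract says the same.
- **Study Design** requires more than 10 pack-years of both current smokers and ex-smokers (the inclusion criteria say 10 or more). Neither sets an upper limit. Never-smokers are those who "smoked less than 100 cigarettes in their lifetime", so their dose is essentially zero.
- **Sampling** plans 500 smokers, 200 ex-smokers and 200 never-smokers.
- **Statistical Analysis** adds a general plan: "A multivariable analysis (generalized linear models) will be conducted to control for confounding". It continues: "The full models will contain all independent effects and some important interactions". The models are then reduced by backward elimination, with the Akaike criterion defining the optimal model. This section mentions neither ECG outcomes nor pack-years, and does not say how it relates to the set named under Electrocardiography.
- **Introduction** says that some comorbidities share risk factors with COPD, smoking and ageing above all. It makes comorbidities in the three groups, and their interaction with COPD, a study objective.

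**The concern.** By the article's own account smoking is a plausible common cause of COPD and of heart disease. A three-level status treats a participant with 12 pack-years and one with 50 as equally exposed. Among current smokers, those with COPD are likely to have smoked more. If heavier smoking also makes an abnormal ECG more likely, COPD and ECG abnormality will be associated within each status level even where neither affects the other.

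An odds ratio above 1 from this model could then be read as COPD-related cardiac disease, which touches a stated objective. The variable that would reduce the problem is already in the database.

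**Working it through.** **1. What the plan itself computes.** It gives no figure for the COPD-ECG association. Its only design figures are the precisions in Sampling, which reproduce as 1.96 × √(p(1−p)/n):

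| n | p | computed | stated |
|---|---|---|---|
| 500 | 20% | 3.51% | 3.5% |
| 200 | 10% | 4.16% | 4.2% |
| 200 | 2% | 1.94% | 1.9% |

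They do not bear on confounding, but they supply the group sizes and prevalences used below.

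**2. Bias when dose is left out.** A simulation used the planned 200:200:500 mix scaled up 400 times (360,000 records), COPD at 2%, 10% and 20% in never-, ex- and current smokers, and no true effect of COPD on the ECG. These inputs are assumed and not in the documents: ECG abnormality in 10% overall, pack-years with median 22 and 5th-95th percentiles 13-55 among smokers, and the dose effects in the table. Sex and age were not simulated.

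| COPD OR per 10 pack-years | ECG OR per 10 pack-years | COPD-ECG OR, status only | status + pack-years |
|---|---|---|---|
| 1.2 | 1.0 | 1.00 | 1.00 |
| 1.2 | 1.1 | 1.04 | 1.00 |
| 1.2 | 1.2 | 1.10 | 1.00 |
| 1.2 | 1.3 | 1.17 | 1.00 |
| 1.4 | 1.0 | 1.02 | 1.02 |
| 1.4 | 1.1 | 1.06 | 0.97 |
| 1.4 | 1.2 | 1.19 | 0.99 |
| 1.4 | 1.3 | 1.32 | 1.00 |

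The simulation error of a log OR is about 0.322/√400 = 0.016 (0.322 is derived in step 4), so 0.97 and 1.02 are compatible with 1. The two rows with no dose effect on the ECG show that dose is the mechanism.

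**3. A second set of assumptions.** Among ever-smokers only, with COPD and ECG abnormality each 20% at mean dose and a pack-year SD of 10-15, the spurious OR was 1.04-1.10 for dose ORs of 1.2 and 1.2, 1.06-1.14 for 1.3 and 1.2, and 1.14-1.34 for 1.5 and 1.3. As a hand check, the log of the spurious OR is roughly the product of the two log dose effects and the dose variance, in units of 10 pack-years:

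- ORs 1.2 and 1.2: 0.182 × 0.182 × 1 = 0.033 (OR 1.03) at SD 10; × 2.25 = 0.075 (OR 1.08) at SD 15.
- ORs 1.5 and 1.3: 0.405 × 0.262 × 1 = 0.106 (OR 1.11) at SD 10; × 2.25 = 0.239 (OR 1.27) at SD 15.

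The approximation falls somewhat below the simulated values but gives the same order of size.

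**4. Size against sampling error.** The planning figures imply 500 × 0.20 + 200 × 0.10 + 200 × 0.02 = 100 + 20 + 4 = 124 COPD cases and 776 others. Crude standard error of the log OR:

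- ECG abnormality 10% (assumed): √(1/12.4 + 1/111.6 + 1/77.6 + 1/698.4) = 0.322
- ECG abnormality 20% (assumed): √(1/24.8 + 1/99.2 + 1/155.2 + 1/620.8) = 0.242

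The 95% interval is therefore the OR multiplied and divided by exp(1.96 × 0.242) = 1.6 to exp(1.96 × 0.322) = 1.9. With a two-sided 5% test (sidedness is not stated) and b = ln(OR)/SE, the false-positive rate is P(|Z + b| > 1.96):

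| spurious OR | ln(OR) | b | false-positive rate |
|---|---|---|---|
| 1.04 | 0.039 | 0.12-0.16 | about 5% |
| 1.10 | 0.095 | 0.30-0.39 | 6-7% |
| 1.32 | 0.278 | 0.86-1.15 | 14-21% |

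These use the crude standard error; the adjusted one would usually be larger and the inflation a little smaller.

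**The case against.** The best defence is that the Electrocardiography sentence is a reporting statement in a measurement section and does not exclude further models. The Statistical Analysis section plans models to control confounding that start from all independent effects, and the Discussion says that the important covariates are measured so that adjustments can be made. Pack-years could enter by that route. This stands to the extent that a reader might infer a closed set, and the text does not say that. It does not remove the point. The general plan names neither the ECG analysis nor pack-years, its elimination step could drop pack-years, and an analyst who follows the named set as written leaves dose out.

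The bias is also conditional. It needs a dose-ECG gradient within status levels, which no figure in the documents supports. The exclusion of participants with coronary insufficiency or arrhythmia under regular medication may weaken such a gradient. Age is in the adjustment set and may absorb part of any dose difference that tracks age. The Discussion disclaims causal inference. All of this stands and limits how strongly the point can be put.

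The remedy is imperfect too: a linear term may misfit, and questionnaire pack-years carry reporting error. Residual confounding would shrink but might not vanish.

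**Conclusion.** The point holds as a specific, inexpensive improvement to a stated adjustment set. Smoking status cannot equalise dose among the 700 ever-smokers, and a collected measure of dose is absent from the set. If dose raises the risk of both COPD and ECG abnormality, the COPD-ECG odds ratio is moved away from 1. The spurious OR is about 1.04 to 1.3 under assumed dose effects, ECG rates and pack-year spreads, and about 1.0 if dose does not affect the ECG. The lower end is lost in sampling error; only the strongest assumed effects raise the error rate materially.

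Three stronger readings are not supported. A reader might infer that nothing but smoking status is adjusted for, but sex and age are in the set. A reader might infer that a material bias is established, but its size rests wholly on assumptions and it concerns a secondary association, not the prevalence aim. A reader might extend the point to the associations of COPD with physical findings, but the Physical Exam section names no adjustment set, so nothing there is stated wrongly.

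**What to change.** In the Electrocardiography section, name the adjustment set as sex, age, smoking status and pack-years. Code pack-years as the deviation from the ever-smoker mean for smokers and ex-smokers, and as 0 for never-smokers. Centring does not change the COPD coefficient, because the shift is absorbed by the status terms; it keeps the dose term from duplicating the contrast between ever- and never-smokers. Add one sentence saying that the backward elimination in the Statistical Analysis section does not remove pack-years from this model, so that the two sections agree.

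The cost is one degree of freedom and the assumption of a linear dose effect on the model scale. No new data are needed, and the article describes data processing and analysis as still under way. The Physical Exam section needs no change on this account.

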#### Physical Exam

Clinical investigators were trained to conduct the pulmonary (percussion and inspection) exam and technique for listening to second heart sounds. Two Stanford Medicine 25 modules were used as study materials in hands-on sessions [37,38]. The prevalence of individual pathological findings will be presented for each study group. Associations between pathological findings from 2 exams and COPD will be evaluated.

#### Anthropometry

Anthropometry measures include height, weight, waist circumference, heart rate, blood pressure, and pulse oximetry.

#### Six-Minute Walk Test

All study subjects will take a 6-minute walk test to evaluate functional exercise capacity. Investigators assess whether contraindication exists or not. Absolute contraindications are unstable angina and myocardial infarction during the previous month. Relative contraindications are blood pressure more than 180/100 mm Hg and a resting heart rate of more than 120 beats per minute [39]. Subjects with any of the contraindications are referred to the clinical coordinator for a decision about the conduct of the test. Posttest dyspnea is measured using the Borg scale [40].

#### Laboratory Data

Serum from each participant is tested for blood cholesterol level, high-density lipoprotein (HDL), low-density lipoprotein (LDL)), triglycerides, C-reactive protein, fibrinogen, glucose, hepatitis B and C IgM and IgG antigens and antibodies, alanine aminotransferase (ALT) and aspartate aminotransferase (AST) liver enzymes, and α_1_-antitrypsin.

#### Questionnaire

The questionnaire was designed to collect data on possible COPD risk factors including history of smoking; current smoking; level of smoking exposure (in pack-year); passive smoking; and occupational and environmental hazards including dusts, chemicals, and indoor fuel pollution. The questionnaire contains the following covariates: age, gender, ethnicity, education, occupation, and self-reported morbidity. CAT is used to collect Information about COPD symptoms. The test was designed and validated for use in routine clinical practice to evaluate the health status of patients with COPD [41]. Computer-assisted personal interviewing (CAPI) with tablets has been implemented to collect, store, and transmit data related to a personal survey interview.

The questionnaire was piloted by interviewing 7 testers—3 smokers, 2 ex-smokers, and 2 never-smokers. After completing pilot interviews, the testers were asked to answer specific questions and then provide comments and suggestions on the whole questionnaire. The questions that were not clear enough were identified and have been improved.

### Statistical Analysis

Data from all CAPI devices will be exported to one database, and R version 3.3.1 (The R Foundation) will be used for data analysis. Descriptive analyses will be performed using mean, median, interquartile interval, and standard deviation for quantitative variables and frequency tables for categorical variables. Depending on the nature of outcome and exposure variables, type of data distribution, and the sample size, bivariate comparisons will be made by the following tests: chi-square test, Fisher’s exact test, analysis of variance, *t* test, and the Mann-Whitney test.

A multivariable analysis (generalized linear models) will be conducted to control for confounding. Presence of effect modification/interaction terms will be explored. An alpha <.05 will be considered significant. To construct the optimal model, backward elimination will be used. The full models will contain all independent effects and some important interactions. Mediators (variables that lie on the causal pathway between exposure and outcome) will not be included in the model. To avoid multicollinearity, we will examine the tolerance for each independent variable. If the tolerance value is less than 0.1, we will omit a variable from the analysis. The optimal model will be defined based on the Akaike Information Criterion. Model diagnostic plots will be generated to test model assumptions (eg, normality of deviance residuals).

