Comorbidities are frequently found in persons with COPD. Some of them have risk factors, which are the same as for COPD, particularly tobacco smoking and aging. Moreover, systemic inflammation and chronic hypoxia present in COPD patients may cause other health-related conditions. Common comorbidities include heart disease, lung cancer, osteoporosis, metabolic syndrome and diabetes, anemia, anxiety, cognitive decline, and sleep disorders [21,22]. Specific comorbidities increase mortality and poor outcome in COPD, so management of main comorbidities has been included to COPD guidelines [6].

The aim of the study is to assess the prevalence of COPD among smokers, ex-smokers, and never-smokers aged 40 to 59 years based on pulmonary function assessment (spirometry), structural changes (emphysema and large and small airway inflammation with thickening) identified by high-resolution CT, COPD symptoms, and exercise limitations. In addition, the study objectives include comparing the prevalence of health conditions considered as COPD comorbidities (heart disease, hypertension, metabolic syndrome, diabetes mellitus) in 3 study groups and their interaction with COPD.

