### Sampling

According to the Burden of Obstructive Lung Disease (BOLD) protocol, a minimal sample size of 600 is recommended to achieve an acceptable level of precision for estimating COPD prevalence [29]. Our goal is for a sample size of 900 including 500 smokers, 200 ex-smokers, and 200 never-smokers. We have used the National Health and Nutrition Examination Surveys data to assume COPD prevalence in these 3 groups [30]. The sample size of 500 allows for achieving the precision of 3.5% with the expected prevalence of obstructive impairment of 20%. The sample size of 200 and the expected prevalence of pulmonary obstruction of 10% and 2% among ex-smokers and never-smokers, respectively, provides sample estimates with 4.2% and 1.9% precision, respectively [31].

The 3 study groups are planned to have the same gender and age distribution by implementing age-gender quota to eliminate age and gender potential confounding effect to the associations between smoking status and outcomes.

It was shown that the sample characteristics depend on recruitment method used [32]. To recruit study participants, active and passive approaches are used. Participants are recruited by using personal networks of investigators and persons who are already participating in the study (snowball), placing an advertisement of the study in social media (Facebook) targeting those individuals who are potentially eligible to participate (live in Almaty, specific age group), and meeting with the owners and managerial staff of several large companies located in Almaty to explain the benefits of participation in the study. Employees of these companies who are potentially eligible to participate in the study are contacted by phone calls.

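### At the plan's own rates about 4 never-smokers have COPD, so ordinary maximum-likelihood models inflate odds ratios against never-smokers by about 12%, and any interaction of smoking group with a binary factor would often have no finite estimate

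*Protocol article*

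**What the plan says.** The Sampling section sets the group sizes: "Our goal is for a sample size of 900 including 500 smokers, 200 ex-smokers, and 200 never-smokers". It assumes 20% obstruction in smokers and "the expected prevalence of pulmonary obstruction of 10% and 2% among ex-smokers and never-smokers, respectively". It justifies the two smaller groups by saying that this "provides sample estimates with 4.2% and 1.9% precision, respectively". The sizing concerns prevalence precision within each group and nothing else.

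The Statistical Analysis section fixes the model class: "A multivariable analysis (generalized linear models) will be conducted to control for confounding". Effect modification is to be explored, and "The full models will contain all independent effects and some important interactions". The models are then reduced by backward elimination, with AIC defining the optimal model and a 0.05 significance level. The interactions are not named.

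The Introduction adds a secondary objective: to compare comorbidities "in 3 study groups and their interaction with COPD". The Discussion treats the effect of smoking on COPD as the exposure effect whose robustness will be tested in a sensitivity analysis.

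**The concern.** The model class is stated, and so are the expected case counts, but the two fit poorly where never-smokers enter a model of binary COPD. Maximum-likelihood log-odds are biased away from zero when events are few, and the never-smoker group is the likely reference for smoking odds ratios. Every such ratio then carries the reference group's bias.

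A second problem arises if smoking group is crossed with a binary factor such as a comorbidity, dust exposure or passive smoking. The 4 expected cases are split again. If all of them fall on one side of the factor, the logistic coefficient diverges. The output then shows an enormous odds ratio with an unusable standard error, and this could be reported as absence of effect modification when the method could not have detected any.

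**Working it through.** **Inputs from the Sampling section:** n = 500, 200, 200; p = 0.20, 0.10, 0.02. **Assumed, because the article gives no value:** prevalence q of the binary factor (10% to 50%) and its odds ratio with COPD (1, then 2 and 3).

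**1. The plan's own precisions.** Half-width = 1.96 × √(p(1−p)/n).
- Smokers: 1.96 × √(0.2 × 0.8/500) = 3.51%, printed 3.5%.
- Ex-smokers: 1.96 × √(0.1 × 0.9/200) = 4.16%, printed 4.2%.
- Never-smokers: 1.96 × √(0.02 × 0.98/200) = 1.94%, printed 1.9%.

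All three reproduce, so these rates are the design inputs and the printed precisions are not in question.

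**2. Expected cases.** 500 × 0.20 = 100; 200 × 0.10 = 20; 200 × 0.02 = 4; total 124. Among never-smokers, P(no case) = 0.98^200 = 1.8% and P(at most 2 cases) = 23.5%.

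**3. Bias of the main effect.** For x ~ Binomial(200, 0.02), average log(x/(200−x)) over samples with x ≥ 1 and subtract the true value log(0.02/0.98). The result is −0.110. A reference log-odds that is 0.110 too low multiplies the odds ratios by exp(0.110) = 1.12.

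The same sum gives −0.004 for smokers and −0.023 for ex-smokers. Net of these, the inflation is exp(0.110 − 0.004) = 1.11 for smokers and exp(0.110 − 0.023) = 1.09 for ex-smokers. In the 1.8% of samples with no never-smoker case, the odds ratio itself is not finite.

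For scale, the standard error of the log odds ratio of smokers against never-smokers is about √(1/100 + 1/400 + 1/4 + 1/196) = 0.52, so the bias is about a fifth of it.

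In this one-factor model the Firth correction amounts to adding 0.5 to each cell. Averaging log((x+0.5)/(200−x+0.5)) over all samples, including x = 0, leaves a bias of −0.002. On the samples with x ≥ 1 alone it is +0.035.

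**4. Empty cells if smoking group is crossed with a binary factor.** With no association, the chance that the never-smoker cases all fall on one side of the factor, or that there are none, is (1 − 0.02q)^200 + (1 − 0.02(1−q))^200 − 0.98^200. At q = 10% this is 0.670 + 0.026 − 0.018 = 0.68.

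| Factor prevalence q | 10% | 20% | 30% | 50% |
|---|---|---|---|---|
| OR 1 | 68% | 47% | 34% | 25% |
| OR 2 | 50% | 31% | 25% | 31% |
| OR 3 | 40% | 26% | 26% | 40% |
| OR 1, never-smoker rate 4% | 45% | 20% | 9% | 3.5% |
| OR 1, never-smoker rate 6% | 30% | 9% | 3% | 0.5% |

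For OR 2 and 3, q is the prevalence among people without COPD, and the formula uses the corresponding prevalence among cases.

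A simulated binomial model of a comorbidity on group, COPD, their product, age and sex (N = 900, 600 runs per setting, OR 1) diverged in 72%, 44%, 30% and 23% of runs at the same four values of q, at the 2% rate.

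**5. Where the problem sits.** At q = 10% and OR 1, the empty-cell risk is 13% in ex-smokers and essentially zero in smokers. An association of a factor with COPD that is not split by smoking group uses all 124 expected cases and is usually estimable.

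**The case against.** The strongest objection is that the article never commits to a term crossing COPD with smoking group. The interactions are unnamed, and choosing the important ones leaves room to omit those that the data cannot support. The comorbidity objective may mean simple association: the Electrocardiography section plans associations with COPD in which smoking status is an adjuster. All of this stands. A reader might infer that the plan will fit such interactions, or that the comorbidity objective cannot be answered by the stated method. The text supports neither inference.

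No Wald test is named either. AIC uses the maximised likelihood, which stays finite when a coefficient diverges, so it would be wrong to say that the plan's test can never reject. The estimates and their standard errors remain unusable in that case.

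Sizing on prevalence precision matches the main aim, so the sample size is not at fault. The 2% refers to obstruction, while the aim also draws on CT and symptoms, so the COPD count may be higher and both problems smaller. The check on deviance residuals suggests that continuous outcomes may also be modelled, and these are not affected.

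Finally, handling of sparse cells is commonly left to an analysis plan, which is not shown. Silence on it is therefore no fault. The point rests on the stated model class and the stated rates, and the bias of the main effect arises whether or not any interaction is fitted.

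**Conclusion.** The point holds in limited form.

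- **Main effects.** Odds ratios for binary COPD against never-smokers are inflated by about 12% through the reference group (11% for smokers and 9% for ex-smokers, net). This assumes the 2% rate, never-smokers as reference and a logistic model. It is modest next to the sampling error, but systematic and avoidable.
- **Interactions, conditionally.** If one of the unnamed interactions crosses smoking group with a binary factor, it has no finite estimate in about 25% to 68% of samples (factor prevalence 50% to 10%, no association, 2% rate). The risk falls clearly if never-smoker COPD is more common.
- **Outside the point.** Analyses that do not cross smoking group, and the prevalence estimates themselves, are not called into question.

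**What to change.** In the Statistical Analysis section, state that models of binary COPD that include smoking group, and any interaction involving smoking group and COPD, use Firth penalised likelihood with profile-likelihood intervals and tests. State also that never-smoker-specific interactions on binary COPD are reported as descriptive only. Since AIC is built on the ordinary likelihood, add a sentence on how terms are selected in the penalised models.

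The continuous FEV1/FVC ratio may be analysed as a supplement. It should not replace the COPD analysis, because it answers a question on a different scale.

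The cost is a few sentences and an existing R package. The Results section reports that recruitment is complete, so an analytic remedy is the practical one, and it needs no new participants or data. The downside is slight shrinkage of the estimates. Penalisation keeps estimates finite but does not supply information that 4 cases lack, so intervals involving never-smokers will stay wide.

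### Backward elimination by AIC and an automatic tolerance cut-off, with no protected terms, work against the confounding control that the models are meant to give

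*Protocol article*

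**What the plan says.** The Statistical Analysis section of the protocol article gives the purpose of the models: "A multivariable analysis (generalized linear models) will be conducted to control for confounding". The rules for reaching the final model follow:

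- Starting model: "The full models will contain all independent effects and some important interactions".
- Selection: "To construct the optimal model, backward elimination will be used", and "The optimal model will be defined based on the Akaike Information Criterion".
- Collinearity: "To avoid multicollinearity, we will examine the tolerance for each independent variable". The consequence is automatic: "If the tolerance value is less than 0.1, we will omit a variable from the analysis".

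The only rule based on a variable's role leaves mediators out. No variable is named as always kept, and nothing says which of several collinear terms is to go.

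Three other places bear on this. The Sampling section sets age-gender quotas "to eliminate age and gender potential confounding effect to the associations between smoking status and outcomes". The Electrocardiography section names a fixed adjustment set (sex, age and smoking status) for the COPD-ECG associations. The Discussion states that known important confounders are measured so that the analysis can adjust for them.

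**The concern.** A confounder belongs in the model because of its relation to exposure and outcome, not because it improves fit in this sample. AIC keeps a one-parameter term only if it lowers the deviance by more than 2. With about 124 expected COPD cases, a real confounder of modest strength will often miss that bar. The adjustment set then depends on the data, and standard intervals from the selected model treat it as if it had been fixed in advance.

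The tolerance rule is a separate problem. Tolerance depends on how terms are coded. Shifting the origin of age leaves the fit of an interaction model unchanged but can move a main effect's tolerance from well above 0.1 to far below it. Applied without exemption, the rule could omit a variable for a reason unrelated to its role.

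At stake are the adjusted smoking-COPD estimates and, more so, the COPD-comorbidity associations.

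**Working it through.** **Inputs from the Sampling section.** Groups of 500 smokers, 200 ex-smokers and 200 never-smokers, with expected prevalences of 20%, 10% and 2%. The stated precision reproduces as 1.96·√(p(1−p)/n): 3.51%, 4.16% and 1.94%, against 3.5%, 4.2% and 1.9%. Expected cases: 500×0.20 + 200×0.10 + 200×0.02 = 100 + 20 + 4 = 124.

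**Assumptions not in the documents.** Age uniform from 40 to 60, sexes 50:50, both independent of smoking group (the quota). A binary confounder present in 20/30/40% of never-, ex- and current smokers. The effect sizes below are also assumed.

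**1. Elimination.** Logistic model, n = 900, 1,500 runs. A single term is dropped from the full model if its likelihood-ratio χ² is below 2 (AIC) or below 3.84 (p > .05). The second rule is shown because the article does not say which governs each step.

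| True effect | Dropped, AIC | Dropped, p > .05 |
|---|---|---|
| Confounder, OR 1.3 | 53% | 73% |
| Confounder, OR 1.5 | 27% | 47% |
| Confounder, OR 2.0 | 3% | 7% |
| Age, OR 1.3 per 10 years | 46% | 67% |
| Age, OR 1.5 per 10 years | 17% | 36% |
| Sex, OR 1.2 | 69% | 85% |
| Sex, OR 1.5 | 26% | 46% |
| Smoking status (one factor) | 0% | 0% |

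The Monte Carlo standard error of the 27% is √(0.27×0.73/1500) ≈ 1.1 points.

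Leaving the confounder out moves the median smoker-versus-never OR from 12.0 to 12.7 (confounder OR 1.3), from 11.6 to 12.6 (OR 1.5) and from 11.1 to 12.7 (OR 2.0), or about 6%, 8% and 14%. The confounder that matters most is also the one least often dropped.

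**2. Tolerance.** Tolerance = 1 − R² = RSS/TSS, with RSS and TSS the residual and total sums of squares of the column regressed on the other columns. For the smoker indicator, TSS = 900×(5/9)×(4/9) = 222.2.

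- *Main effects only.* RSS = 1/(1/200 + 1/500) = 142.9, so tolerance = 0.64. Age and sex are near 1.0.
- *Smoking-by-age products, age uncentred.* The indicator is now a contrast at age 0, so its variance is multiplied by 1 + mean²/variance = 1 + 50²/33.3 = 76. RSS = 142.9/76 = 1.88, so tolerance ≈ 0.0085. The ex-smoker indicator and both products are about the same.
- *The same model, age centred.* The multiplier returns to 1, so tolerance = 0.64; the products have 0.29 and 0.50.
- *Age-by-sex, age uncentred.* For sex, RSS = 1/((1/450 + 1/450)×76) = 2.96 and TSS = 225, so tolerance = 0.013.
- *Smoking by two 10-year age bands.* The lowest is the smoker product: RSS = 1/(2×(1/100 + 1/250)) = 35.7 and TSS = 900×(250/900)×(650/900) = 180.6, so tolerance = 0.20. Smoking-by-sex with equal sexes has the same structure and gives about 0.20.
- *Smoking by four 5-year bands.* The lowest is the band indicator: RSS = 1/(2/50) = 25 and TSS = 900×0.25×0.75 = 168.75, so tolerance = 0.15.
- *Overlapping smoking codings.* The Questionnaire section collects smoking history, current smoking and pack-years. Ever, current and ex indicators together are exactly collinear (tolerance 0). Pack-years beside smoking group (assumed mean 25, minimum 10, SD 5 to 15) gives the smoker indicator 0.10 to 0.41. At SD 5 it is 0.104, just above the cut.

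**3. Where the quota helps.** It balances age and sex across smoking groups, so dropping them changes the smoking-COPD contrast little. It does not balance them between people with and without COPD, so it gives no such protection to a COPD-comorbidity model. No simulation was run for those models; this step is reasoning from the design.

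**The case against.** The strongest objection is that forced terms and coding choices are usually left to a full protocol or analysis plan, which is not shown here, and that the Discussion already states the intent to adjust. It does not dispose of the point. The article is not silent: it prints automatic rules without exception, and those rules run against that intent. A fuller plan could still qualify them.

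A reader might infer that the rules will delete the smoking exposure. The documents do not support this. Elimination removed smoking status in none of the simulated runs. The tolerance route needs uncentred continuous-age products or overlapping codings, and the article names neither. It lists independent effects separately from interactions, so the check may be meant for main effects only, where the smoking indicators have 0.64. Banded age and smoking-by-sex terms also stay above 0.1. This part of the objection stands.

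It also stands that quotas limit the harm to the smoking-COPD contrast, that the ECG analysis has its own fixed set (though this is not reconciled with the general rule), and that the drop rates rest on assumed effects.

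A reader might also infer a demonstrated loss of interval coverage. A 250-run simulation gave 94% for the full model and 92% after selection, with Monte Carlo standard errors of about 1.5 and 1.7 points. That difference is within noise. The argument about intervals is therefore one of principle, without a measured size.

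**Conclusion.** The point holds in a limited form. Data-driven elimination with no protected terms conflicts with the stated aim of confounding control. Under the assumptions above, AIC discards a real confounder in about a quarter of runs at OR 1.5 and about half at OR 1.3, and it can discard age or sex. The resulting shift in the smoking-COPD odds ratio is modest, about 6% to 8% for those two confounders. The COPD-comorbidity associations other than ECG are more exposed, because the quota does not protect them.

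The tolerance rule is a conditional hazard: tolerance of about 0.01 for smoking status or sex with uncentred continuous-age products, or 0 with fully redundant smoking codings, and no breach otherwise in the forms checked.

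Two further inferences are not upheld. Normality of deviance residuals is given only as an example, for generalized linear models that may include continuous outcomes. Sparse never-smoker cells would become acute only in an age-by-sex breakdown that the article does not propose.

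**What to change.** 1. Keep smoking group, age, sex and a fixed list of measured confounders (passive smoking, dust, chemical and fuel exposure, education, ethnicity) in every association model.
2. Do not use backward elimination for those estimates. At most, use AIC to choose among exploratory interactions, and label them as such.
3. Centre age and pack-years before forming products.
4. Exempt the forced terms and all product terms from the tolerance rule.
5. State how the general rule relates to the fixed adjustment set in the Electrocardiography section.

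The article's Results section reports that data processing and analysis are under way, so the change should be dated and made before the association models are run. It needs only wording, and no new data. The downside is slightly wider intervals than a stepwise model would show.
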